##### Secondary outcomes

Binomial outcomes including rehabilitation referrals, pneumonia, PPOI, unplanned ICU admissions, patient-reported complications, and mortality will be analysed using multivariate robust random effects Poisson generalised linear regression.Time-to-event binomial outcomes (e.g. PPC, pneumonia, PPOI, achievement of ambulation goals of 1 and 10 min; and hospital and ICU LOS; and mortality) will be compared by estimating hazard ratios using Cox proportional hazards regression, with and without covariate adjustment where necessary and graphically illustrated using Kaplan-Meier methods.Measures involving estimation of rate of change over time (QOL and functional capacity) will be analysed using repeated-measures mixed effects linear regression or ordered logistic regression for rank-ordered scale measures.Hospital costs will be compared using mixed effects linear regression. Log transformation of highly skewed cost data will be performed. Depending on the adequacy of the data for purposes of economic analysis, a cost-utility may be conducted.

All outcomes will be analysed on an intention-to-treat basis. An intention-to-protocol sensitivity analysis will be performed by identifying as a separate group participants who received more than 80% of planned protocol sessions as per group allocation. Other planned sensitivity analyses will be made according to age (> 65), surgery type (colorectal, upper gastrointestinal, other), preoperative self-reported physical capacity, and gender. Sensitivity of outcome estimates to missing data will be evaluated using multiple imputations. All analyses will be performed using Stata MP2 V14 (StataCorp, College Station, TX, USA).

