**Discussion:**

The morbidity, mortality, and fiscal burdens following emergency abdominal surgery are some of the worst within surgery. Physiotherapy may be an effective, low-cost, minimal harm intervention to improve outcomes and reduce hospital utilisation following this surgery type. ICEAGE will test the benefits of this commonly provided intervention within a methodologically robust, multicentre, double-blinded, active-placebo controlled randomised trial.

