#### Secondary/exploratory trial outcomes

In hierarchical order:Referral by the surgical team or other allied health professional within the first 14 postoperative days for additional acute-ward physiotherapy rehabilitation, sub-acute hospital rehabilitation, or community-based rehabilitation. On receipt of a referral, or by the 14th postoperative day if referral not received, a blinded senior physiotherapist will review the participant’s current medical record and adjudicate for the requirement for rehabilitation services.Discharge destination from the acute hospital ward (home, rehabilitation facility, nursing home, or other hospital);Hospital LOS in days. This is defined as continuous days spent in any type of inpatient hospital service (i.e. acute care, sub-acute rehabilitation, or time at another hospital) from the day of admission for acute condition to the day of discharge to community. Hospital days will be sub-categorised into acute and sub-acute;Incidence of a prolonged postoperative ileus (PPOI) anytime from the fourth to the 14th postoperative hospital day. A PPOI is defined if two or more of the following criteria are met on or after the fourth postoperative day [30]: (i) nausea or vomiting, (ii) inability to tolerate an oral diet over last 24 h, (iii) absence of flatus over the last 24 h, (iv) abdominal distension, and (v) radiologic confirmation. The day which PPOI is first diagnosed is the day of PPOI onset for purposes of time-to-event analysis.Diagnosis of pneumonia defined as the presence of new CXR infiltrates along with at least two of the following: temperature > 38 °C, dyspnoea, cough, and purulent sputum, altered respiratory auscultation, and white cell count > 14,000/ml or leukopenia < 3000/ml on any day within the first 14 postoperative hospital days;Recovery of physical function and QOLi)Rate of change of the Modified Iowa Level of Assistance [31] (mILOA; Additional file 1) score over four measures taken second daily from the first postoperative day and a final score on the day of acute-ward discharge. The mILOA consists of four mobility tasks (supine to sitting on the edge of the bed, sit to stand, walking, and negotiation of one step), which are graded according to the level of assistance required, use of gait aid, and the distance that can be walked. Data will be extracted from the medical and physiotherapy records to score;ii)Rate of change in handgrip strength (kg) measured using a handheld dynamometer over four postoperative measures within the first 14 days. Measures will be taken at least 2 days apart;iii)Rate in change of the EuroQual QOL score [32] (EQ-5D; Additional file 2); measures to be taken directly from the patient over two consecutive measures separated by 48 h, within the first five postoperative days, and at 90 days following surgery;iv)Health-related QOL using World Health Organisation Disability Assessment Schedule V2 [33] (WHODAS; Additional file 3) change from self-rated status in the week prior to surgery, to day of discharge from acute care, and at 90 days following surgery;v)Physical capacity using Self-Assessment of Physical Activity Questionnaire [34] (SAQ; Additional file 4) from self-rated capacity regarding the week prior to surgery to 90 days following surgery;vi)Time in hours from end of operation to time able to achieve ambulation greater than 1 min;vii)Time in days from end of operation to achieve ambulation greater than 10 min;ICU LOS in days;Unplanned ICU admission during acute hospital stay;Mortality—in-hospital, 30 and 90days, and at 1 year;Sepsis within the first 7 days according to the Sequential Organ Failure Assessment (SOFA) for ICU patients and quick-SOFA for ward patients [35];Time in days to discharge from physiotherapy as determined daily using the Post-Operative Physiotherapy Discharge Scoring Tool [18] (Additional file 1);Time in days to readiness for hospital discharge within the first 14 postoperative days defined by standardised scoring criteria [36];Patient reported complications at 90 days using a standardised semi-structured interview [16];Hospital costs for the admission episode of care supplied by the participating centres’, or health departments’, costing data for each participant’s admission episode.

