### Protocol endpoints

Treatment protocols will be ceased when:Participant is discharged or transferred from the primary treating hospital.Participant becomes deceased or death is expected within next 7 days.Participants meet a threshold score to trigger discharge from physiotherapy treatment^18^. This criterion is delayed for the first five postoperative days for intervention participants.A confirmed PPC diagnosis ceases the respiratory treatment protocol. Respiratory treatment is then provided at the discretion of the ward physiotherapist. Participants remain being treated with the rehabilitation protocol as per group allocation.A confirmed referral for additional sub-acute rehabilitation services ceases the ambulation or early rehabilitation protocol. Rehabilitation is then provided at the discretion of the ward physiotherapist. Participants remain being treated with the respiratory treatment protocol as per group allocation.

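### Hospital length of stay ends at discharge to the community but is plotted by Kaplan-Meier with no provision for in-hospital death, so with deaths censored the curve overstates the proportion discharged

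*Protocol article*

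**What the plan says.** Under Secondary/exploratory trial outcomes, the protocol article defines hospital LOS as "continuous days spent in any type of inpatient hospital service", counted "from the day of admission for acute condition to the day of discharge to community". It is third in the stated hierarchy. ICU LOS in days appears further down the list.

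Under Statistical methods, Secondary outcomes, both stays are named as time-to-event outcomes: "hospital and ICU LOS; and mortality) will be compared by estimating hazard ratios using Cox proportional hazards regression". They are to be "graphically illustrated using Kaplan-Meier methods". The same section states: "All outcomes will be analysed on an intention-to-treat basis".

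Death in hospital is foreseen. Mortality is a secondary outcome, measured "in-hospital, 30 and 90days, and at 1 year". Protocol endpoints lists as a reason to stop the treatment protocols: "Participant becomes deceased or death is expected within next 7 days". The abstract describes the setting in words only: "The morbidity, mortality, and fiscal burdens following emergency abdominal surgery are some of the worst within surgery".

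The article does not say how a stay that ends in death enters the LOS analysis. It names no competing-risk method and no cumulative incidence curve.

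**The concern.** The event that ends LOS is discharge to the community, and in-hospital death makes that event impossible. Kaplan-Meier treats a censored participant as someone who could still have the event later. Applied to a death, this counts a dead participant as still able to go home, and the curve climbs above the proportion who were in fact discharged. No difference between the arms is needed for this to happen.

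The hazard ratio raises a related problem of interpretation. With deaths censored, it compares the rate of discharge among those still alive in hospital. A reader will probably take it as an effect on the chance of going home, which also depends on how many die. Mortality is an outcome of the same intervention, and the abstract's discussion offers lower hospital utilisation as a possible benefit, so the LOS result should not leave survival out of view.

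**Working it through.** **The plan's own figures.** The article gives no in-hospital mortality rate, no median stay and no precision for LOS, so there is no LOS figure to reproduce. Its only power figure, 131 per group for 20% versus 8%, does reproduce (two-sided 0.05, 80% power, pooled variance, no continuity correction), but it has no bearing on this point.

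**Inputs.**
- Planned total 288, so 144 per arm (Sample size section).
- Assumed: constant discharge hazard a = 0.075 per day, which gives 1 − exp(−0.075 × 14) = 65% at day 14.
- Assumed: in-hospital death proportion m of 3%, 5%, 10% or 15%, with constant death hazard b = a × m/(1 − m).

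**Formulas.**
- One minus Kaplan-Meier with deaths censored: 1 − exp(−a t).
- True proportion discharged alive: a/(a + b) × (1 − exp(−(a + b) t)), where a/(a + b) = 1 − m.
- Standard error (SE) of the true proportion p in one arm: sqrt(p(1 − p)/144).

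**Day 30.** One minus Kaplan-Meier is 1 − exp(−2.25) = 89.46% in every row.

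| Mortality | b per day | Discharged alive | Excess (points) | SE (points) |
|---|---|---|---|---|
| 3% | 0.00232 | 87.46% | 2.0 | 2.8 |
| 5% | 0.00395 | 86.11% | 3.4 | 2.9 |
| 10% | 0.00833 | 82.61% | 6.8 | 3.2 |
| 15% | 0.01324 | 78.98% | 10.5 | 3.4 |

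(The excess is taken before rounding.)

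**Other days.** At day 14 the excess is 0.9, 1.5, 3.0 and 4.7 points, against an SE of about 4.0. At day 90 it is 3.0, 5.0, 9.9 and 14.9 points, which is close to the death proportion itself.

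**A different discharge hazard.** With log(2)/10 per day, the day-30 excess is 3.1, 6.4 and 9.9 points at 5%, 10% and 15% mortality. The picture does not depend on the choice of 0.075.

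**Reading the hazard ratio.** Take equal discharge hazards, with 10% mortality in control and 5% in intervention. The cause-specific hazard ratio is 1.00 and the two Kaplan-Meier curves coincide. Yet the proportion discharged alive by day 30 is 82.6% versus 86.1%, a difference of 3.5 points that neither planned output shows. In a simulation of this setting with discharge hazard log(2)/10, the subdistribution hazard ratio was about 1.12.

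**Deaths entered as end of stay.** With the same hazards, the ratio for leaving hospital by either route is (a + b₁)/(a + b₀) = (0.075 + 0.00395)/(0.075 + 0.00833) = 0.947. At 15% versus 5% it is 0.85/0.95 = 0.895, and at equal mortality it is 1.00. If every stay ends in an event, the SE of the log ratio is about sqrt(2/144) = 0.118. Since |log 0.947| = 0.054, the shift at 10% versus 5% is 0.054/0.118 = 0.46 SE.

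**The case against.** A reader might infer that the planned Cox ratio is itself wrong, or that the analysis fails however deaths are coded. The documents do not support that, for three reasons.

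- Cox regression with deaths censored gives a valid cause-specific hazard ratio for discharge.
- A third coding avoids both faults. Deaths can be kept at risk to the longest follow-up as never discharged. With complete inpatient follow-up, Kaplan-Meier then reproduces the cumulative incidence, and Cox gives essentially the subdistribution ratio. The article does not state this coding, but it does not rule it out.
- A reader might also infer that early deaths will be scored as short stays, so that an intervention that saves lives looks slower to get people home. The written definition ends the stay at discharge to the community, and a death is not that. Such coding would contradict the definition, and even with mortality halved from 10% to 5% it moves the ratio by less than half an SE.

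The size can also be questioned. The 2 to 10 points are bias in a single-arm curve and largely cancel in the comparison if mortality is similar in both arms. At day 14 the excess is less than half an SE (about 2.0 points) for mortality of 3% and 5%. Eligibility excludes patients approaching imminent death or withdrawal of treatment within 48 hours of surgery, which favours the lower part of the assumed range. Mortality is reported separately, so an imbalance would be visible.

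All of this stands and limits the point. It does not remove it. Coding rules are often left to a statistical analysis plan, but here the article itself fixes the endpoint, the model and the graph. Under the usual censoring, that graph is wrong for that endpoint.

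**Conclusion.** The point holds in a limited form. With deaths censored, the Kaplan-Meier plot overstates the proportion discharged in each arm, by 2.0 to 10.5 points at day 30 for in-hospital mortality of 3% to 15%. The Cox ratio remains valid as a cause-specific ratio but says nothing direct about the probability of discharge.

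The sizes rest on assumed mortality, constant hazards and about 65% discharged by day 14, because the article gives no rates. A false contrast between arms on the curves, or a distorted ratio if death counted as exit, further requires unequal mortality.

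This is a worthwhile, low-cost improvement to a secondary outcome. The primary comparison of pulmonary complication rates is not affected.

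**What to change.** - State that the event for hospital LOS is live discharge to the community and that in-hospital death is a competing event.
- Replace the Kaplan-Meier plot for hospital LOS with the cumulative incidence of live discharge by arm.
- Keep the planned Cox ratio, label it cause-specific, and report beside it a subdistribution hazard ratio in which deaths stay at risk as not discharged.
- Do the same for ICU LOS, with live ICU discharge as the event and death in ICU as competing.

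The cost is analysis wording. The LOS and mortality outcomes already require discharge and death dates, and Stata, the named package, has the routine. Recruitment was still open when the article was published, so the change could be made before unblinding. The downside is one more estimate to report and interpret.

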### Trial setting

The three participating centres represent a range of hospital types in Australia. The Launceston General Hospital (Launceston, Tasmania, Australia) is a regional primary referral hospital; the Princess Alexandra Hospital (Brisbane, Queensland, Australia), a metropolitan primary referral hospital; and Northeast Health Wangaratta (Wangaratta, Victoria, Australia), a sub-regional secondary referral hospital, are all government-funded, university-affiliated, teaching hospitals.

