### Randomisation and allocation

An administrative assistant independent of the trial will prepare 288 consecutively numbered (1 to 288) opaque envelopes each containing an allocation card wrapped in extra paper or aluminium foil [14]. Allocation sequence is determined by a computer-generated (http://www.randomizer.org/) blocked random number table (6 blocks of 48) with large blocks to minimise guessing of allocation sequence. The randomisation table will be sealed in an opaque envelope, locked within the primary centres’ research institute, and made unavailable to trial personnel until trial completion. The number of consecutively numbered envelopes provided to each site will be dependent on funding agreements (i.e. funded to recruit one block of 48 participants, or, on a per patient recruit basis till the end of the trial).

Once a patient has been deemed eligible, the treating ward physiotherapist receives the group allocation by first writing patient details on the next consecutively numbered sealed opaque envelope and then opening it. If numerous new patients are eligible on the same day at a site, envelopes will be allocated in alphabetical order of surname. If an envelope is not available at the time of randomisation, a coin can be tossed by the treating physiotherapist and the result written on a card and countersigned by an independent observer. This card will be placed within the envelope that should have been allocated for that patient. If an envelope is erroneously opened out of sequence, the reason for doing so will be documented on it and the patient will be treated as per allocation card. Any aberrations to sequential allocation will be recorded. Envelopes will be kept securely by the ward physiotherapist or site investigator until hospital discharge and then integrated with the consent form and filed securely by the site investigator. Potential selection bias will be studied by extracting basic demographic data and planned surgical procedure from the medical records of all included and excluded patients.

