#### Other components of postoperative care

Additional ambulation occasions or DB&C sessions conducted independently by the participant or assisted by other ward staff will not be measured nor controlled for as this would not be feasible or consistent with the pragmatic nature of this trial. All other aspects of patient care, including general anaesthesia, surgical techniques, intraoperative ventilation parameters, fluid delivery, prophylactic antibiotic prescription, pain management, use of lines and drains, general nursing care, and discharge planning, will be administered according to routine clinical practice at each participating centre.

The three participating sites have limited physiotherapy service on weekends and on public holidays. If protocol is unable to be delivered due to service limitations, this will be recorded.

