#### Statistical methods

Imbalances of potential confounding variables between trial groups at recruitment will be assessed. Adjustment covariates will be selected by backward stepwise regression from covariates that are anticipated to affect incidence of PPC. These include respiratory comorbidity, smoking history, age, gender, length of operation, operation category (upper gastrointestinal, colorectal, urological, other), and ICU admission immediately following the procedure.

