##### Primary outcome

The absolute and relative rates of PPC in the trial groups will be estimated using multivariate robust random effects Poisson generalised linear regression to allow assessment of binary outcomes with or without adjustment for potential confounding variables (incidence rates and rate ratios, 95% confidence intervals, *p* values). Treatment centre will be treated as a fixed variable in multi-level models. In addition, the effect of time from the end of surgery/anaesthesia to commencement of symptoms of PPC will be compared using Cox proportional hazards regression with and without covariate adjustment (hazards ratio, 95% confidence intervals, *p* values). A Kaplan-Meier graphic representation of this analysis will be performed.

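### The Cox model for hospital length of stay names no centre term; if discharge practice differs materially between the three hospitals, the hazard ratio is attenuated and power is lost

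*Protocol article*

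**What the plan says.** All references are to the protocol article.

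- **Secondary outcomes (Statistical methods).** Time-to-event outcomes "will be compared by estimating hazard ratios using Cox proportional hazards regression, with and without covariate adjustment where necessary". The outcomes listed include "achievement of ambulation goals of 1 and 10 min; and hospital and ICU LOS; and mortality".
- **Primary outcome (Statistical methods).** After describing the random-effects Poisson model, the text says: "Treatment centre will be treated as a fixed variable in multi-level models". The next sentence adds a Cox regression for time to a postoperative pulmonary complication (PPC), with and without covariates, and does not mention centre.
- **Statistical methods, opening paragraph.** Covariates are chosen by backward stepwise regression from factors thought to affect PPC incidence: "These include respiratory comorbidity, smoking history, age, gender, length of operation, operation category", and then immediate postoperative ICU admission. Centre is not listed.
- **Other components of postoperative care.** Among the aspects of care left to local practice: "discharge planning, will be administered according to routine clinical practice at each participating centre".
- **Trial setting.** "The three participating centres represent a range of hospital types in Australia": one metropolitan primary referral, one regional primary referral and one sub-regional secondary referral hospital.
- **Randomisation and allocation.** The sequence comes from a "blocked random number table (6 blocks of 48) with large blocks to minimise guessing of allocation sequence". Centre is not named as a stratification factor, and the supply of envelopes to a site depends on its funding agreement.
- **Secondary/exploratory trial outcomes.** These are in hierarchical order, and hospital length of stay is third.

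**The concern.** The plan recognises centre as a factor to model, but its wording ties that to one class of model. The Cox models are not called multi-level, and the covariates offered to them were chosen for their relation to PPC, not to discharge. Read as written, length of stay would be analysed over three hospitals with one pooled baseline hazard.

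Omitting a prognostic factor from a Cox model moves the treatment hazard ratio toward 1 even when the factor is perfectly balanced between arms, and it disturbs proportionality. The effect grows with the proportion of patients who have the event, so it is greatest for an outcome such as discharge. At stake is the power and interpretation of a highly ranked secondary outcome, when the factor that would protect it is known for every patient.

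**Working it through.** **1. The plan's own figure.** The only power statement is for PPC: 20% v 8%, alpha 0.05, power 80%. With mean risk 0.14:

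n per group = [1.96·√(2·0.14·0.86) + 0.8416·√(0.20·0.80 + 0.08·0.92)]² / 0.12² = (0.962 + 0.407)² / 0.0144 ≈ 130.1, rounded up to 131.

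The total is 262, as stated, and 262 × 1.10 = 288.2 matches 288. No figure is given for length of stay or any other Cox outcome, so what follows rests on assumptions.

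**2. Anchor without centre differences.** With 1:1 allocation, d events and hazard ratio HR, power = Φ(√d/2 · ln HR − 1.96). For d = 288 and HR = 1.4: √288/2 · 0.3365 − 1.96 = 0.895, giving 81%.

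**3. Simulation by centre medians.** Assumptions: 288 patients in centres of 144, 96 and 48; Weibull stay with shape 1.5; within-centre hazard ratio for discharge 1.4; two-sided 5% Wald test. With shape 1.5, a centre with median m has hazard (10/m)^1.5 relative to the 10-day centre. Medians 8/10/13 therefore mean hazards of about 1.40/1/0.67.

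| Centre medians (days) | HR, without v with strata | Power, 1,500 trials, uncensored | Power, 5% censored | Power, 8,000-trial rerun, uncensored |
|---|---|---|---|---|
| 9/10/11 | 1.40 v 1.40 | 79% v 80% | 78% v 78% | 79% v 79% |
| 8/10/13 | 1.38 v 1.41 | 76% v 80% | 72% v 76% | 76% v 80% |
| 7/10/15 | 1.33 v 1.40 | 66% v 79% | 63% v 76% | 67% v 79% |

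Hazard ratios are from the 1,500-trial run, except the first row, which is from the rerun. The losses are 0 to 1, about 4, and 12 to 13 points. With identical centres the rerun gives 80% without strata and 78.5% with strata, so stratifying then costs about 1.5 points.

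**4. Simulation by hazard multiples.** Assumptions: 262 patients, 7% censored, within-centre hazard ratio 1.41, 4,000 trials per scenario.

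| Centre hazards | Equal centres: HR and power, without v with strata | Shares 4:1:1: HR and power, without v with strata |
|---|---|---|
| 1/1/1 | 1.41 v 1.41; 76% v 74% | 1.42 v 1.42; 75% v 75% |
| 1/1.2/0.83 | 1.41 v 1.42; 75% v 75% | 1.41 v 1.42; 76% v 75% |
| 1/1.5/0.67 | 1.38 v 1.42; 69% v 75% | 1.40 v 1.42; 73% v 76% |
| 1/2/0.5 | 1.34 v 1.42; 60% v 75% | 1.36 v 1.41; 66% v 73% |
| 1/3/0.33 | 1.28 v 1.42; 46% v 74% | 1.32 v 1.42; 56% v 75% |

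**5. Type I error.** With a true hazard ratio of 1, the model without centre rejects in about 5 to 6% of trials in every scenario.

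**6. Uncommon events.** The PPC rates imply a hazard ratio of ln(0.92)/ln(0.80) = 0.374. With 262 patients and control risk 10 to 20%, power with and without strata differs by at most about 2 points, and the hazard ratio by about 0.01, even at centre hazards 1/2/0.5.

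**The case against.** **The text is silent, not wrong.** No sentence excludes centre from the Cox models. The centre sentence stands between the Poisson and Cox descriptions and could be meant as a general rule, the covariate list is introduced as inclusive, and strata for secondary models are often left to an analysis plan. This stands in part: a reader might infer that the plan has decided against a centre term, and the document does not say that. But it does state a rule for centre and limits it by its wording, so the scope of that rule is a fair point.

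**The loss is not shown.** This stands. A reader might infer that power will be lost. The documents give no distribution of stay, centre sizes or between-centre difference, and at medians of 9/10/11 days the loss is nil. The largest median-based loss needs one hospital's median to be more than twice another's. Stay also counts sub-acute days and time at another hospital, so the acute ward's routine does not determine it alone.

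**Not every Cox model is affected.** This stands. A reader might extend the point to PPC, pneumonia and mortality, but for uncommon events the effect is negligible. The ambulation goals come in because nearly all patients are likely to reach them, not because of discharge practice; ambulation follows a standardised protocol.

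**Validity is not threatened.** This also stands. The shift is between a marginal and a within-centre hazard ratio, not confounding. Allocation names no stratification by centre, although a site supplied with one full block would be blocked internally.

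**Conclusion.** The point holds in a limited form. As worded, the centre rule reaches the multi-level models only, and the Cox model for length of stay names no centre term although local discharge routines make centre a likely determinant. If the centres differ materially, the hazard ratio is attenuated and power falls: by about 0, 4 and 12 points across the three sets of medians, and by up to 28 points at a three-fold hazard step with equal centres. These sizes rest on an assumed within-centre hazard ratio of about 1.4, 93 to 100% of patients having the event, and assumed centre sizes and differences. This is a question of efficiency and clarity for a secondary outcome. It does not bear on the primary Poisson analysis.

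**What to change.** Under Secondary outcomes, state that the Cox models for hospital length of stay, and for other time outcomes that nearly all patients reach (for example the two ambulation goals), are stratified by treatment centre in both the unadjusted and the adjusted versions: a separate baseline hazard for each centre and one common treatment effect. This brings them into line with the centre rule under Primary outcome and should be fixed before outcome data are seen by arm. On these grounds no change is needed for PPC or other uncommon events.

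The cost is one sentence and a standard Cox model option, with no new data and no design change. If the centres do not differ, about 1 to 2 points of power are given up.
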